**Secondary (exploratory) outcomes**
• AAA diameter (mm) and volume (cm^3^)
• Agatston score of AAA
• Aortic aneurysmal wall CT values (mm^3^, %)

AAA, abdominal aortic aneurysm; CT, computed tomography; MACE, major adverse cardiovascular events.

Additionally, AAWCV—the total volume of regions with specific CT values and their proportions to the AV—will be evaluated in mm^3^, and percentages, respectively. The 6 ranges mostly encompass all aneurysm components: (i) -100 ≤ Hounsfeld units (HU) < -40; (ii) -39 ≤ HU < -10; (iii) -9 ≤ HU < 20; (iv) 21 ≤ HU < 50; (v) 51 ≤ HU < 80; and (vi) 81 ≤ HU. AAWCV will be evaluated within each range above and in the early and delayed phases of contrast-enhanced CT imaging.

### Criteria for cessation of the protocol treatment

Tricaprin administration will be discontinued, and urgent surgical intervention will be considered if any of the following occur: aneurysmal diameter increases by ≥ 5 mm over a 6-month period or MMSD exceeds 51 mm on CT scans asymptomatically; AAA-related abdominal symptoms develop; or imaging evidence suggests impending rupture, even without symptoms. The need for urgent surgical intervention will be assessed in all patients who meet these criteria. However, participants meeting these criteria may opt to continue tricaprin use until the day of surgery.

### Determination of the target for data analysis

The full analysis set will be used for data analysis, including all patients, excluding ineligible cases, with at least one tricaprin administration of 3.0 g/d and visit, regardless of treatment discontinuation during the follow-up period. A sensitivity analysis of secondary endpoints will be scheduled for participants with good compliance to medication use, defined as a tricaprin consumption rate > 60%. This threshold is based on phase 2a trial data,^29^ which showed that patients with triglyceride deposit cardiomyovasculopathy who maintained a tricaprin intake of ≥ 1.5 g/d showed improved clinical outcomes. If participants consume > 60% of tricaprin throughout the trial period, they will have ingested an average daily dose exceeding 1.8 g/d. Therefore, individuals in the sensitivity-analysis group should be considered to have received a dose sufficient to assess tricaprin efficacy.

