### Study design

This is a single-centre, open-label, and single-arm trial designed to investigate the safety of oral tricaprin 3 g/d for patients with AAA and explore potential indicators of efficacy. Patients with AAA who meet all the inclusion criteria and no exclusion criteria will be eligible for enrollment. A schematic representation of the trial is shown in Figure 1. Candidates will be recruited from an outpatient population diagnosed with asymptomatic infrarenal AAA. Tricaprin safety will be evaluated for all adverse events throughout the trial period. Additionally, efficacy indicators will be explored using abdominal CT findings. No post-treatment follow-up evaluation is planned.

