### Treatment protocol and study assessments

All participants will receive 1.5 g/d tricaprin for the first 2 weeks until visit 1, after which the dose will be increased to 3.0 g/d and maintained until week 52, administered in 3 divided doses per day. Participants unable to tolerate this increase will be excluded from further analyses. Lifestyle management, smoking cessation, and adjustment of metabolic and cardiovascular medications will be encouraged. Participants will visit the investigator quarterly to assess their symptoms, their experience of MACE, aneurysmal exacerbations, and side effects based on vital signs, adverse events, medication compliance, concomitant medication use, safety tests, and abdominal CT scans. Visits from visit 2 onward will be scheduled approximately every 3 months, with a 14-day flexibility period allowed. Contrast-enhanced and unenhanced CT scans at screening and visit 5 will measure the aneurysmal diameter, volume, Agatston score, and AAWCV. Visit 3 will include an unenhanced CT scan to check for abrupt expansion (≥ 5 mm over 6 months). Electrocardiograms will be conducted at the beginning and end of the trial to screen for asymptomatic cardiovascular complications. Tricaprin consumption will be monitored at each visit by using a patient diary and measuring the change in the weight of the tricaprin bottle. A tricaprin consumption rate of > 60% will be set as the threshold for the secondary endpoint sensitivity analysis. Figure 2 outlines the trial process (patient flowchart). Table 2 presents the data collection schedule.

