**Figure 2 fig2:**
[figure not shown]
Patient flowchart. The patient flowchart outlines the trial process. All participants who provide informed consent will undergo screening tests. Patients will be excluded if they are found to be ineligible based on screening, unable to tolerate the increase in tricaprin from 1.5 to 3.0 g/d, show concerning computed tomography (CT) findings at visit 3, experience severe adverse events, request withdrawal, or are deemed ineligible at any visit for other reasons. AAA, abdominal aortic aneurysm; MMSD, maximum-minor short-axis diameter After initiating tricaprin use at 3, ∗ After initiating tricaprin use at 3.0 g/d, the trial may be discontinued if any abnormal findings warrant cessation, even between scheduled visits.

**Table 2 tbl2:** Data collection schedule

Study item, data collection, or activity	Informed consent	Screening visit	Day 0	Day 1	Visit 1	Visit 2	Visit 3	Visit 4	Visit 5	Cessation
Day of performance, d	—	–56 to –1	0	1	14	91	182	273	364	—
Allowance period, d	—	—	—	—	± 7	± 14	± 14	± 14	± 14	+ 28
Informed consent	X	X	—	—	—	—	—	—	—	—
Patient’s background	—	X	—	—	—	—	—	—	—	—
Eligibility confirmation	—	X	—	—	—	—	—	—	—	—
Tricaprin administration, g	—	—	—	1.5	➡	3.0	➡	➡	➡	—
Adherence check	—	—	—	—	X	X	X	X	X	X
Comorbidities/Medical history	—	X	—	—	—	—	—	—	—	—
Abdominal contrast CT scan	—	X	—	—	—	—	—	—	—	X
Abdominal unenhanced CT scan	—	X	—	—	—	—	X	—	—	X
Clinical findings		X	X	—	X	X	X	X	X	X
Laboratory test		X	X	—	X	X	X	X	X	X
Electrocardiogram		X	—	—	—	—	—	—	X	X
Adverse events		—	—							

The shorter arrows indicate the same dosages as those shown on the left side of each one. The longer arrow represents the continuous monitoring of adverse events between visits.

CT, computed tomography.

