### Study endpoints and statistical assessments

The primary endpoint is the safety of oral tricaprin for 52 weeks, as determined by analysis of the occurrence rate of adverse events, specifically the following: (i) MACE incidence; MACE includes cardiovascular death, nonfatal myocardial infarction, and nonfatal stroke.; (ii) AAA exacerbation; adverse events related to AAA exacerbation include nonfatal acute abdomen with proven AAA rupture, nonfatal acute abdomen without overt AAA rupture, a sudden change in skin color, or edema of the lower limbs with severe pain, and an abrupt need for surgical intervention; and (iii) unpredictable tricaprin side effects; unpredictable tricaprin side effects include miscellaneous events presumably related to tricaprin use and not attributable to (i) or (ii). These events will be assessed via physical examinations, vital sign assessments, safety laboratory tests, physiological tests, and abdominal CT scans. In particular, for MACE, AAA exacerbation, and unpredictable side effects following administration of tricaprin, the number of occurrences and events and their percentages will be calculated and presented, apart from the total analysis of all adverse events, owing to their clinical importance. Additionally, vital sign measures and laboratory test results will be summarized with descriptive statistics at each visit as a subanalysis. Vital signs include the following: systolic blood pressure (mm Hg); mean blood pressure (mm Hg, calculated using the formula [diastolic pressure + (systolic – diastolic) / 3”]; and heart rate (beats per minute). Laboratory test results will include measures of levels of alanine aminotransferase, gamma-glutamyl transpeptidase, blood urea nitrogen, creatinine, sodium, potassium, chloride, D-dimer, C-reactive protein, and brain natriuretic peptide; a complete blood cell count (white, red, hemoglobin, hematocrit, and platelets); and estimated glomerular filtration rate.

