### Sample size calculation and statistical considerations

A sample size of 10 participants was selected based on ethical considerations and the exploratory nature of the study. Although medium-chain triglycerides have a well-established safety profile, the safety of tricaprin in patients with AAA remains unverified. Moreover, including many participants in an initial safety assessment trial is unethical. AAAs are clinically diverse, with varying progression rates, and no established efficacy endpoints. Although MMSD is used frequently, sometimes it may not increase over extended periods.^35^ This variability makes the establishment of its clinical significance challenging. Given these factors and the lack of spontaneous reverse remodelliing in AAAs, we have opted not to perform statistical significance tests. Instead, we will summarize our findings using descriptive statistics.

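### The only analysis set, which also serves the primary safety endpoint, leaves out treated participants who never reach or cannot tolerate 3.0 g/d

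*Protocol article*

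**What the plan says.** The Protocol article, Study endpoints and statistical assessments, defines the primary endpoint: "The primary endpoint is the safety of oral tricaprin for 52 weeks, as determined by analysis of the occurrence rate of adverse events". Table 3 lists all adverse events as the primary outcome. Study design promises the same scope: "Tricaprin safety will be evaluated for all adverse events throughout the trial period".

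Under Treatment protocol and study assessments, every participant takes 1.5 g/d for two weeks up to visit 1, then 3.0 g/d to week 52. The Figure 1 legend gives the purpose of those two weeks as excluding unexpected side effects.

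Two rules then decide who is analysed:

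- Determination of the target for data analysis names one main population, the full analysis set, and does not limit it to efficacy. It takes eligible patients "with at least one tricaprin administration of 3.0 g/d and visit, regardless of treatment discontinuation during the follow-up period". Stopping later thus does not remove a participant from the set.
- Treatment protocol and study assessments: "Participants unable to tolerate this increase will be excluded from further analyses". The Figure 2 legend lists those "unable to tolerate the increase in tricaprin from 1.5 to 3.0 g/d" among the patients who will be excluded.

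The only other population named is participants with more than 60% consumption, and it is for secondary endpoints. No population of all treated participants is stated.

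**The concern.** In a safety trial, the population should be fixed by exposure and not by how well the exposure was tolerated. Here, entry to the analysis requires a participant to have got through the starting dose, and a separate sentence removes those who fail the increase. Both conditions are likely to select on the primary outcome itself.

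Two results are at stake. The adverse event rate and the rate of stopping for adverse events would both be understated whenever early stopping is caused by an event. And because the two rules disagree about some participants, the denominator of the main result could be settled after the data are seen. With 10 participants, a single case decides whether the report says that one participant could not tolerate tricaprin or that there were no events.

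**Working it through.** **There is no sample size calculation to reproduce.** The article says: "A sample size of 10 participants was selected based on ethical considerations and the exploratory nature of the study". It gives no event rate, alpha or power, and "we have opted not to perform statistical significance tests". The check therefore compares the rules and then works through what they do to a rate based on 10 participants.

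**Step 1. Apply each rule to each type of treated participant.**

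| Treated participant | Full analysis set | Intolerance rule | All adverse events, whole trial |
|---|---|---|---|
| Stops for an event at 1.5 g/d, never takes 3.0 g/d | Out | Not clearly addressed | Should count |
| Takes 3.0 g/d, attends a visit, stops because the increase is not tolerated | In | Out | Should count |
| Accepts 3.0 g/d, stops later in follow-up | In | Not addressed | Counts |
| Takes tricaprin, later found ineligible | Out, read literally | Not addressed | Should count |

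The first row follows from the analysis set definition alone. The second row is a direct conflict between two sections. In Table 2, dosing starts on day 1, visit 1 is day 14 (± 7 days) and visit 5 is day 364. The 52 weeks of the primary endpoint therefore include the period at 1.5 g/d.

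**Step 2. How often would someone be dropped?** Let p be the chance that a participant fails to reach or tolerate 3.0 g/d and is excluded. The documents give no value, so a range is assumed. With 10 treated, P(at least one dropped) = 1 − (1 − p)^10.

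| Assumed p | Expected number dropped (10p) | P(at least one dropped) |
|---|---|---|
| 5% | 0.5 | 40% |
| 10% | 1 | 65% |
| 20% | 2 | 89% |
| 30% | 3 | 97% |

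**Step 3. What happens to the reported rate?** Suppose k of 10 have a related event and are dropped, and nobody else has an event. Intervals are exact (Clopper–Pearson) 95%. For x events in n, the lower limit is the 0.025 quantile of Beta(x, n − x + 1) and the upper limit is the 0.975 quantile of Beta(x + 1, n − x). For x = 0 the lower limit is 0 and the upper limit is 1 − 0.025^(1/n); for example, 1 − 0.025^(1/9) = 33.6%.

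| k | All treated | As the rules report it |
|---|---|---|
| 1 | 1/10 = 10% (0.3–44.5%) | 0/9 = 0% (0–33.6%) |
| 2 | 2/10 = 20% (2.5–55.6%) | 0/8 = 0% (0–36.9%) |
| 3 | 3/10 = 30% (6.7–65.2%) | 0/7 = 0% (0–41.0%) |

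**Step 4. Relax the assumption of no other events.** With one further participant with an event among those retained, k = 1 gives 1/9 = 11.1% instead of 2/10 = 20%, and k = 2 gives 1/8 = 12.5% instead of 3/10 = 30%. The contrast is no longer zero against non-zero, but the rate is still understated.

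**The case against.** The strongest reply is that the analysis set definition does less than it seems to. It keeps anyone who took 3.0 g/d once and had a visit, even if that person then stopped. Only those who stop before the increase, in roughly 14 of 364 days, or who have no qualifying visit are lost. Excluding those who fail the increase depends on the other sentence, and its reference to further analyses could mean only that later assessments stop, with earlier events still reported. The Figure 2 legend may describe patient flow and not removal of data. Study design also gives the aim as the safety of 3 g/d, which a set requiring that dose would fit. The full protocol or analysis plan, not shown here, may define a safety set. Finally, the zero rates assume no other events, and dropping an early withdrawal who had no event would raise the rate (1/9 = 11.1% against 1/10 = 10%).

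Much of this stands as a limit on size. Intolerance that appears after an accepted increase is counted under the analysis set definition, Figure 2 is weak support, and the figures are illustrations.

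It does not rescue the rule. Even on the mildest reading of the intolerance sentence, a participant who stops for an event at 1.5 g/d is outside the only set defined, although that period exists to detect such events. The narrower aim in Study design sits beside a promise to evaluate all adverse events throughout the trial, and the Abstract describes treatment as 1.5–3.0 g/d for 52 weeks. A safety set in an unseen document would mean that the article misstates it. The lack of significance tests is no defence, because a descriptive rate is biased by the same exclusion.

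**Conclusion.** The concern holds: the rule is wrong as written and must be fixed. Two parts are firm. The sole analysis set, applied to the primary safety endpoint without restriction, omits participants treated only at 1.5 g/d. The sentence on intolerance contradicts that set for participants who took 3.0 g/d, had a visit and then stopped.

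One intolerant participant in 10 can turn a reported rate of 10% into 0%, and two can turn 20% into 0%. These figures assume that the dropped participants are excluded (at the 1.5 g/d stage by the analysis set, or at the increase by the intolerance sentence), that each had a related event, and that nobody retained had one. The chance of losing at least one participant is 40% to 97% over an assumed exclusion rate of 5% to 30%. The direction is downward whenever early stopping is linked to adverse events, which is the case that matters in a tolerability assessment.

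**What to change.** 1. In Determination of the target for data analysis, add a safety set: all participants who took at least one dose of tricaprin at any level, including any later found ineligible. Use it for the primary endpoint and for every safety summary.
2. Count adverse events from the first dose and tabulate them by dose at onset (1.5 or 3.0 g/d), so that the result at 3.0 g/d can still be read separately.
3. Keep the requirement of a 3.0 g/d administration for the secondary CT analyses only.
4. In Treatment protocol and study assessments, remove the exclusion from analysis of those who cannot tolerate the increase. Report the number who fail to escalate, with reasons, as a safety result.
5. State in the Figure 2 legend that its exclusions concern patient flow and do not remove safety data.

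This changes the analysis population and its wording only; no dose or treatment rule is affected. Adverse events are already monitored continuously, so no extra data are needed. The one consequence is that the reported adverse event rates may be slightly less favourable. The change should be recorded before the data are analysed.

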### Sample size calculation and statistical considerations

A sample size of 10 participants was selected based on ethical considerations and the exploratory nature of the study. Although medium-chain triglycerides have a well-established safety profile, the safety of tricaprin in patients with AAA remains unverified. Moreover, including many participants in an initial safety assessment trial is unethical. AAAs are clinically diverse, with varying progression rates, and no established efficacy endpoints. Although MMSD is used frequently, sometimes it may not increase over extended periods.^35^ This variability makes the establishment of its clinical significance challenging. Given these factors and the lack of spontaneous reverse remodelliing in AAAs, we have opted not to perform statistical significance tests. Instead, we will summarize our findings using descriptive statistics.

### Time frame

Patient recruitment began on May 17, 2024, and it is expected to be completed by November 30, 2024. The study is anticipated to be completed by March 31, 2026.

### Study organization

The trial was designed by the Laboratory of Cardiovascular Disease, Novel, Non-invasive, and Nutritional Therapeutics (CNT), Department of Triglyceride Science, Graduate School of Medicine, Osaka University, Osaka, Japan. The Department of Cardiovascular Surgery and Cardiovascular Medicine at Osaka University Hospital will propose a backup plan for patient enrollment and the management of emergency cases. The Department of Radiology at Osaka University Hospital, will analyze the CT images. Data management, statistical analysis, and monitoring will be performed at the Department of Medical Innovation, Osaka University Hospital, Osaka, Japan, as part of the second Clinical Research Support Project of Osaka University Hospital. The Tochino Foundation will provide all investigational substances at no cost. The authors are responsible for the trial conception, manuscript preparation and editing, and final content.

### External committee

The trial will be conducted in compliance with the ethical principles of the Declaration of Helsinki and the Clinical Research Act. Approval was obtained from the Osaka University Clinical Research Review Committee on May 9, 2024, with the approval number of CRB5180007. Written informed consent will be obtained from all participants. The trial registration number is jRCTs051240036 from the Japan Registry of Clinical Trials. No patients with AAA were engaged in developing the study protocol or steering the committee.

## Discussion

### Study rationale, implication, and anticipated results

This study aims to provide new insights into the pathophysiology of AAA and treatment gaps using a unique evaluation method. We expect to establish the safety of tricaprin use for treating patients with AAA, and we propose a clinically feasible pathologic evaluation method using the AAWCV and the Agatston score.

In the aortic hypoperfusion model, tricaprin administration significantly reduced aneurysm diameter to near-normal levels and demonstrated high vasa vasorum patency with minimal proliferation. We also observed decreased hypoxia-inducible factor 1α levels and improved vascular smooth muscle cell function and abundance.^23^ These findings suggest that tricaprin use can maintain aortic wall blood flow via the vasa vasorum, enhance medial smooth muscle cell function, and reduce lipid accumulation. To validate the effects of tricaprin on AAA, histologic confirmation of the improved blood flow and lipid reduction in human specimens is necessary. Because of the challenges in obtaining human AAA specimens from patients undergoing follow-up care, establishing noninvasive evaluation methods is essential. We aim to verify the potential of the AAWCV for evaluating aortic wall contrast as a substitute for pathologic analysis, as lipid reduction and blood flow improvement are expected to alter the contrast CT values within the aortic wall.

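### Ten participants in a single arm can describe adverse events but cannot establish or confirm the safety of tricaprin: no event in 10 leaves a rate of about 31% possible

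*Protocol article*

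**What the plan says.** The section on study rationale, implication and anticipated results states: "We expect to establish the safety of tricaprin use for treating patients with AAA". The Abstract likewise describes the trial as one meant to confirm safety in small AAA.

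The design behind those statements is modest. Under Study design: "This is a single-centre, open-label, and single-arm trial designed to investigate the safety of oral tricaprin 3 g/d for patients with AAA". Under Sample size calculation and statistical considerations: "A sample size of 10 participants was selected based on ethical considerations and the exploratory nature of the study". The primary endpoint is set out as follows: "The primary endpoint is the safety of oral tricaprin for 52 weeks, as determined by analysis of the occurrence rate of adverse events". For the events singled out as clinically important (MACE, AAA exacerbation and unpredictable side effects), "the number of occurrences and events and their percentages will be calculated and presented". The authors add that "we have opted not to perform statistical significance tests" and continue: "Instead, we will summarize our findings using descriptive statistics".

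The article gives no acceptable event rate, threshold or precision target for safety. Study limitations acknowledges the small sample and the short period, but the explicit caution there concerns efficacy. On safety, that section relies on animal work, marketing experience and trials in another disease.

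**The concern.** The conclusion announced in advance is stronger than the design can give. Without a control arm, events caused by tricaprin cannot be separated from the background events of an older population with vascular disease. With 10 participants, even a clean result in a given category leaves common harms possible.

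The article calls the trial a foundation for larger ones. If a result of 0% for MACE or AAA exacerbation is reported under the heading of safety established, that reading can pass into the planning and consent material of the next trial, although the data would not support it.

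**Working it through.** **The plan's own figure.** The article gives no precision, power or event-rate calculation for the 10 participants, so there is nothing to reproduce. The check asks what 10 participants can show.

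**Inputs**
- n = 10, one arm, no control (Study design; Sample size calculation and statistical considerations).
- Follow-up of 52 weeks, taken as about 10 person-years in total (Study endpoints and statistical assessments).
- Background rupture in small AAA: 0.04 per 100 person-years, or below 5% per year (opening paragraph of the introduction).
- Assumption, not in the article: 95% confidence with exact binomial (Clopper-Pearson) limits.
- Assumption, for illustration: true event rates of 5%, 10% and 20%.

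**Step 1. Upper limit when a category has no event**
- Two-sided 95%: 1 − 0.025^(1/10) = 0.308, that is 30.8%.
- One-sided 95%: 1 − 0.05^(1/10) = 0.259, that is 25.9%.
- Other methods give similar answers: rule of three 3/10 = 30.0%; Wilson 27.8%.
- With only 9 or 8 participants in the analysis, the two-sided exact limit becomes 33.6% or 36.9%.
- One event in 10 gives an exact two-sided 95% interval of 0.3% to 44.5%.

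**Step 2. Chance of missing a real event entirely, (1 − p)^10**

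| True rate p | Calculation | Chance of no event in 10 |
|---|---|---|
| 5% | 0.95^10 | 60% |
| 10% | 0.90^10 | 35% |
| 20% | 0.80^10 | 11% |

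**Step 3. Rupture, at both of the article's figures**
- At the 5% per year ceiling: 0.95^10 = 0.599, so about 60% of such trials see no rupture.
- At 0.04 per 100 person-years: 10 × 0.0004 = 0.004 ruptures expected, and 0.9996^10 = 0.996, so over 99% see none.

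Anywhere in that range, no rupture is the likely result even if tricaprin does nothing.

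**Step 4. Scale.** To exclude a rate p with zero events, n must be at least ln(α)/ln(1 − p). The value of α is 0.05 for a one-sided 95% limit and 0.025 for a two-sided one.
- p = 10%: 29 participants (one-sided) or 36 (two-sided).
- p = 5%: 59 or 72.

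These numbers show how far 10 is from establishing safety. They are not a proposal to enlarge the trial.

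**The case against.** **It is only a sentence in the Discussion.** No decision rule depends on it. Elsewhere the aims are milder: to evaluate, investigate or examine safety. The sample size section presents the trial as exploratory and as a first safety assessment. This is right as far as it goes, and it makes the point one about the stated conclusion, not about the conduct of the trial. But the Abstract repeats the strong form, and the limitations section does not temper it for safety.

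**Intervals belong in the SAP.** A reader might infer that the plan has decided against confidence intervals. The article does not support that: it declines significance tests and promises descriptive statistics, and exact intervals fit with both. An SAP that is not shown may include them, so their absence here is not the defect. Intervals would show the imprecision but would not make 10 participants enough to establish safety.

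**The 31% is not for all adverse events.** A reader might apply it to the whole primary outcome. It holds only for one category in which nobody has an event. Having no adverse event of any kind in 52 weeks is unlikely at this age.

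**The wall CT-value measure (AAWCV).** A reader might infer a parallel fault, that AAWCV is to be verified as a replacement for histology without any tissue. The text says less: "We aim to verify the potential of the AAWCV for evaluating aortic wall contrast as a substitute for pathologic analysis". It speaks of potential, the same section says that confirmation in human specimens is needed, and the section on AAWCV calls the method at most a partial alternative. That criticism is not made here.

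**Readers will see the denominator.** Counts are reported and n = 10 is stated throughout. This lessens the risk of misreading but does not correct a conclusion that the authors themselves state.

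**Conclusion.** The concern holds for the stated safety conclusion. A single arm of 10 participants cannot establish or confirm safety, and the article's caution covers efficacy only. For a single category with no event in 10, the exact two-sided 95% limit is 30.8%, and a harm with a true rate of 10% stays invisible in about one such trial in three.

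The figures assume independent participants, all 10 analysed, and the exact binomial convention named above. The 5%, 10% and 20% rates are illustrations; the rupture range uses both of the article's figures.

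A reader might go further and infer that the sample size is wrong. The documents do not support that: 10 is defensible for an exploratory first study in this population. What needs correcting is the conclusion promised from it.

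**What to change.** 1. In the Discussion and the Abstract, replace the claims to establish and to confirm safety with a statement that the trial will provide a preliminary description of adverse events.
2. State beside it that, for any category with no event among 10 participants, a rate up to about 31% (exact two-sided 95% limit) cannot be excluded.
3. Extend the caution in Study limitations from efficacy to safety.
4. Present the planned percentages for adverse events, MACE, AAA exacerbation and side effects with exact Clopper-Pearson 95% intervals, based on the number of participants with at least one event. This is compatible with doing no significance tests. If the SAP already provides for it, nothing more is needed on this item.

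The cost is a line of analysis and some wording. Sample size, conduct and clinical management do not change. The downside is that the stated conclusion becomes less favourable.
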